###### User Experience

In SARA, we maintain a coherent user experience using an aquarium theme throughout the app. For example, in the spatial task, we use seashells to match the aquarium theme instead of flowers originally used by the Apple Research Kit [52,79]; after data collection, rather than only providing memes or life insights, we use animations consistent with the aquarium theme; divers swim into the aquarium and inform the participants that they earned a reward (eg, meme or life insight). Further attention-to-detail is provided to improve user experience; for example, Sunday’s survey contains 2 parts where participants answer a few questions about their day, followed by a few questions about the past week. Since Sunday’s survey is longer than other days, we include a fun question right after the daily questions to entertain and energize participants before asking them additional questions about the past week. This fun question is randomly selected from a set of 5 questions in Multimedia Appendix 7.

With this, we conclude the description of different engagement strategies in SARA. Figure 3 provides a summary of the engagement strategies and how these strategies affect various theoretical constructs to influence self-report completion in SARA.

#### Implementation Details

We used the cross-platform JavaScript framework Ionic to build the Android and iPhone versions of SARA. The aquarium part uses the Phaser 2D game library for the animations. All the self-reported data in SARA are encrypted to comply with the Health Insurance Portability and Accountability Act (HIPAA). All data are stored in Amazon S3, a HIPAA-compliant data storage service, and the communication between Amazon S3 and the mobile phone app is encrypted with RSA 2048 and AES-256 [80].

### Objective

In the previous section, we described several of SARA’s novel engagement strategies. Although SARA engagement strategies were designed to influence self-report completion among youth who use substances, the effectiveness of these strategies is unknown. Important questions include whether different SARA engagement strategies lead to higher self-report completion and how their effectiveness is moderated by context (eg, negative affect, stress, loneliness, etc). Ineffective engagement strategies may aggravate participants, and participants may habituate even to an initially effective engagement strategy [81,82], resulting in a decrease, over time, in the effectiveness of the strategy. Similar drawbacks might occur if an engagement strategy is used in a context in which it is ineffective; indeed, the current context of each participant may influence the effectiveness of an engagement strategy [77]. One way to gain insight into these questions is by experimentally manipulating the engagement strategies over time. In other words, the manipulation can inform the development of a policy for adaptive engagement strategy delivery to keep participants engaged in self-reporting. Recently, MRTs have been proposed as a method to develop JITAIs for mHealth [42,43]. In SARA, the intervention is composed of the engagement strategies, such as giving a meme or issuing an inspirational message. In MRTs, study participants are randomized sequentially, often multiple times a day, to receive different intervention components. Several key elements in MRTs are decision points and proximal outcomes. *Decision points* refer to the time points when participants are randomized. In SARA, there is a 4 pm decision point at which a participant is randomized to receive an inspirational message via push notification or receive nothing. Once a participant is randomized at a decision point, the *outcome* of using an engagement strategy can be measured *proximally*. A proximal measure for the 4 pm inspirational message is whether or not the participant self-reports later on the same day. For more details on MRTs, we refer the readers to [42,43,83]. In the following, we describe the MRT protocol for SARA.

**Figure 3 figure3:**
[figure not shown]
A conceptual diagram of how the different engagement strategies should affect self-report completion.

### Study Protocol

We plan to run a 30-day MRT. Prior to the study, potential participants are screened, and eligible participants complete an in-person intake session with a study recruiter. Within the 30-day study, each participant is randomized at each of 4 decision points per day. After the 30 days, each participant takes part in a follow-up phone interview and provides feedback on using SARA for a month. The details of the study are as follows:

#### Study Setting and Eligibility

The 30-day MRT is conducted at the University of Michigan. Study participants are recruited from the University of Michigan Hospital Pediatric and Adult Emergency Departments. The study is approved by the Institutional Review Board of the University of Michigan Health System (HUM00121553) and is registered at ClinicalTrials.gov (NCT03255317). Patients are eligible for screening if they are aged between 14 and 24 years, understand English, are medically stable, are able to provide informed consent or assent (eg, not cognitively impaired or intoxicated), and are accompanied by a parent or guardian (for patients aged between 14 and 17 years). Individuals are eligible if they 1) have an Android or an iPhone mobile phone on which the app can be downloaded and 2) screen positive for past-month binge drinking (≥4 drinks for females and ≥5 drinks for males, on at least 1 occasion) or past-month cannabis use without a medical marijuana card.

#### Baseline Procedure

At the University of Michigan Emergency Department, recruiters monitor incoming admissions and identify patients in the target age range who do not meet the screening exclusion criteria (eg, presentation for sexual assault, droplet precautions, active vomiting, roomed in critical care). After completing an online consent or assent, participants self-administer a screening survey on a tablet, which contains questions regarding their demographics [84,85], health behaviors such as alcohol and marijuana use [8] and sleep habits [86], cell phone capabilities, and social media use. The screening survey takes approximately 8 min to complete, and participants receive a small gift valued at US $1.00 (eg, headphones, water bottle, mobile phone armband) for completing it. Those who report past-month binge drinking or marijuana use and have access to their mobile phone while in the Emergency Department provide written consent or assent and self-administer an approximately 20-min baseline survey with items about (1) substance use frequency, consequences, overdose, and driving under the influence [86-88]; (2) violence involvement, injury, and risky sex behaviors [6,89-92]; (3) coping and mindfulness [93,94]; (4) social influences [95-97]; and (5) motivation or self-efficacy to reduce their alcohol and marijuana use [98,99].

Then, the recruiters collect contact information from the participants. Recruiters ensure that participants install SARA on their phone during the intake since in the pilot study prior to this trial, we have found that many potential participants did not install the app after they left the intake session. Basic instructions on how to use the app are provided during intake, followed by motivational statements regarding participant’s stated barriers to using SARA regularly. Participants receive US $20 cash for completing their intake visit.

#### The 30-Day Microrandomized Trial

Following the intake session, participants start the 30-day MRT with SARA. Each day, participants are requested to complete 1 survey and 2 active tasks between 6 pm and midnight. Participants are randomized at the following 4 decision points each day:

*4 pm reciprocity notification*: Every day at 4 pm, with a probability of .5, participants are randomized to either receive a push notification with an inspirational message—a song lyric or a quote from a contemporary celebrity—or to not receive anything.*6 pm push reminder notification*: Every day at 6 pm, a reminder notification is issued. The notification may be one of the following 2 types, randomized at .5 probability:A simple reminder to complete a survey and 2 active tasksA reminder to complete a survey and 2 active tasks, along with an additional persuasive message. The additional persuasive message may be one of the following 3 messages:“Do you know it only takes a minute to fill out the survey and active tasks?”“Do you know you can earn money if you complete a 3-day streak?”“You are close to unlocking the next fish for the aquarium.”*Reinforcement after survey completion*: If the survey is completed, participants are randomized at .5 probability to receive or not receive either a meme or a gif as a positive reinforcement. If a reinforcement is delivered, there is a .5 probability to receive a meme and a .5 probability to receive a gif.*Reinforcement after active task completion*: If active tasks are completed, participants are randomized at .5 probability to receive or not receive a life insight as a positive reinforcement.

Note that not all the engagement strategies in SARA are randomized. The randomizations in 1-4 mentioned above are motivated by scientific questions concerning the abovementioned engagement strategies in SARA. Specifically, we randomize the push notifications because they can interrupt the participant and are intrusive, thus potentially reducing engagement. The other engagement strategies are not push notifications, so there is low risk of interruption; for example, the participant decides whether to open the app, complete self-reports, and receive the rewards. We randomize the memes and life insights because of the scientific question of how funny and informative contents respectively can influence self-report completion over time [44].

##### Exit Procedure

Participants are contacted by telephone to complete a 1-month follow-up interview, which includes the identical measures as the screen or baseline or daily survey or Sunday’s survey, as well as the following 2 new threads of questions: (1) a 30-day Timeline Followback calendar, which captures past-month alcohol and marijuana consumption [100] and (2) Likert-type and open-ended questions to capture user experience of SARA [101]. For completing the follow-up interview, participants receive a US $30 electronic gift card of their choice (eg, Amazon, Starbucks, etc).

### Analysis Plan

In this section, we describe the analysis plan to evaluate SARA. A more detailed version of the analysis plan can be found in a Center for Open Science document [102] (submitted on October 23, 2017).

#### Outcome Measures

The proximal outcomes of the randomizations are whether participants completed the survey and active tasks. For the inspirational message notifications at 4 pm and the reminder notifications at 6 pm, the proximal outcome is whether the survey or the active tasks are completed in the evening on the same day. For the 2 reinforcement interventions, the proximal outcome is whether the survey or the active tasks, respectively, are completed on the following day. Note that our engagement strategies are primarily designed to encourage self-reporting on the same or next day. Although the strategies may have longer term effects as well [81,82], we are interested in their effects on the same day or the next day; if these effects are consistently higher, then longer term adherence will be higher too. In addition, poststudy open-ended feedback from the participants will be analyzed to refine future versions of SARA.

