**Conclusions:**

To the best of our knowledge, SARA is the first mobile phone app that systematically manipulates engagement strategies in order to identify the best sequence of strategies that keep participants engaged in data collection. Once the optimal strategies to collect data are identified, future versions of SARA will use this data to provide just-in-time adaptive interventions to reduce substance use among youth.

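### A positive same-day or next-day effect does not imply higher longer-term adherence: delayed burden from past notifications cancels out of the primary contrasts and of the effect-by-time analysis

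*Protocol article*

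**What the plan says.** The Outcome Measures section of the protocol article sets the outcome windows. For the 4 pm and 6 pm notifications, "the proximal outcome is whether the survey or the active tasks are completed in the evening on the same day". For the two reinforcements, "the proximal outcome is whether the survey or the active tasks, respectively, are completed on the following day". It then explains the choice: "Although the strategies may have longer term effects as well [81,82], we are interested in their effects on the same day or the next day", and adds that "if these effects are consistently higher, then longer term adherence will be higher too".

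Elsewhere the article names ways in which a strategy could do harm. The section on the 30-day trial says push notifications are randomised because "they can interrupt the participant and are intrusive, thus potentially reducing engagement". The Objective section says ineffective strategies may aggravate participants and that "participants may habituate even to an initially effective engagement strategy". The Exploratory Analyses section plans to examine how effectiveness changes over time. The abstract's conclusions describe the manipulation of strategies as done "in order to identify the best sequence of strategies that keep participants engaged in data collection".

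**The concern.** The step from proximal effects to longer-term adherence is stated as fact. It holds only if a notification sent today does not lower completion on later days by enough to cancel today's gain. The article's remarks on intrusiveness and aggravation give reason to doubt that.

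The design also hides this kind of harm from the primary contrast. Because "Every day at 4 pm, with a probability of .5, participants are randomized", whatever happened before, the notified and non-notified groups on any day have the same expected number of recent notifications. Burden from those notifications lowers completion equally in both groups and drops out of the difference. The word for consistency in the plan's sentence does not help: the effect can be positive and equal on every day while total completion falls.

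The interpretation is at stake. The article's aim is sustained self-reporting, and under Future Work the data are to train an initial delivery policy. A strategy with a same-day gain and a later loss would look favourable on the proximal contrast alone.

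**Working it through.** The article gives no effect size, power or carry-over figure. The nearest design figure is the alpha for each primary hypothesis, .05/2 = .025, which reproduces but does not bear on this point. The check is therefore one of logic, illustrated with assumed values.

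**Inputs from the article:** 73 participants, 30 days, 4 pm randomisation at probability .5 daily.

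**Assumed, not in the article:** base completion 55%; immediate effect +5 points; each notification costs c points on each of the next three days. With A = 1 if notified,

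P(complete on day t) = 0.55 + 0.05·A(t) − c·[A(t−1) + A(t−2) + A(t−3)].

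**1. What the primary contrast sees.** The bracket is independent of A(t). From day 4 its mean is 3 × 0.5 = 1.5 in both groups. The difference is 5 − c × (1.5 − 1.5) = 5 points for every c.

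**2. What happens to total completion.** Under always sending, the mean bracket over 30 days is (0 + 1 + 2 + 27 × 3)/30 = 84/30 = 2.8. Under never sending it is 0. Always minus never is 5 − 2.8c:

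| c (points) | Proximal contrast | Always minus never |
|---|---|---|
| 1 | +5 | +2.2 |
| 2 | +5 | −0.6 |
| 3 | +5 | −3.4 |

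Break-even is c = 5/2.8 ≈ 1.8 points. Simulation with 200,000 participants gave proximal estimates of 5.0 and policy differences of +2.18, −0.59 and −3.40. Lagged contrasts on the same data recovered the cost per lag.

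**3. Trial size, other assumptions.** 73 people, 30 days, base 60%, immediate effect +6 points, adjustment for previous-day completion, person-clustered standard errors, 400 replicates; policy completion from 20,000 simulated people:

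| Burden per past notification | Proximal estimate | Never | Always |
|---|---|---|---|
| none | 5.9 | 60.0% | 66.0% |
| 2 points × 3 days | 6.1 | 60.0% | 60.4% |
| 0.5 point × 7 days | 6.0 | 60.0% | 62.9% |
| 1 point × 7 days | 6.0 | 60.1% | 60.0% |
| 2 points × 7 days | 5.9 | 60.0% | 53.8% |

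**4. Does the effect-by-time analysis see it?** In these five scenarios the mean slope was about 0 and the test rejected in 4% to 7% of runs at .05, so it does not. For habituation, with the immediate effect falling from +13 to −1.5 points, the mean slope was −0.49 point per day and the test rejected in 48% of runs. The planned analysis is therefore aimed at habituation, with moderate power in that example.

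**5. Precision of a lagged analysis.** With completion near 50%, a contrast of two equal groups over n person-days has SE ≈ 2·√(0.25/n) = 1/√n. Days with three earlier days available number 73 × 27 = 1,971, so SE ≈ 1/√1,971 = 2.25 points for each lag. That is close to the proximal value on all 73 × 30 = 2,190 days, 1/√2,190 = 2.1 points. The four estimates are nearly uncorrelated, so their sum has SD ≈ √4 × 2.25 = 4.5 points. Weighting lags 1 to 3 by 29/30, 28/30 and 27/30, to match the 30-day total, gives √(1 + 0.934 + 0.871 + 0.810) × 2.25 ≈ 4.3 points. A 95% interval is then about ±8 to 9 points (1.96 × 4.3 = 8.4; 1.96 × 4.5 = 8.8).

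**The case against.** The case for the plan has several parts that stand.

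- **Habituation is covered.** A reader might infer that the plan ignores it. It does not: the Objective section describes habituation as a decline over time in a strategy's effectiveness, and Exploratory Analyses examines that decline.
- **The primary analysis is sound.** A reader might infer that the primary tests are invalid. They are not. Proximal outcomes are a key element of a micro-randomised trial, and no hypothesis, alpha level or model rests on the disputed sentence.
- **Nothing shows that burden occurred.** A reader might infer that notifications reduce adherence. The documents give no carry-over figure, and the inference survives mild burden (c = 1 above). Same-evening harm would show in the 4 pm contrast.
- **The worry is narrower than all four components.** The intrusiveness remark concerns push notifications. A 6 pm reminder goes out daily in both groups, and the two reinforcements are randomised only after completion.
- **The article says the trial serves only to optimise further development of SARA,** so adoption of a harmful strategy is not a direct consequence.

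The article also refers to a fuller analysis plan and a methods appendix that are not shown and might contain lagged analyses. So the absence of such an analysis from the article is not itself the fault. But no additional analysis makes the unconditional sentence true, and that sentence is what is challenged.

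**Conclusion.** The concern holds as a fault of inference. The sentence linking proximal effects to longer-term adherence needs an added assumption that past notifications carry no offsetting delayed burden. The same-day and next-day contrasts stand, but neither they nor the effect-by-time analysis can test that assumption.

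In the illustrations, a proximal contrast fixed near 6 points went with a policy effect anywhere from +6 to about −6 points. These sizes rest on assumed base rates, effects and carry-over. They show that the sign can reverse, not that it did. Reversal requires the summed carry-over to exceed the immediate gain. The trial can support statements about same-day and next-day completion. From what the article describes, it cannot by itself support statements about sustained adherence or a best sequence.

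**What to change.** 1. Delete the inference under Outcome Measures, or make it conditional on no harmful carry-over from earlier notifications. Limit claims about sustained adherence and about the best sequence in the same way.
2. Add an analysis, mainly for the 4 pm notification: lag-1 to lag-3 effects on completion, and moderation of the same-day effect by the number of recent notifications. Label it exploratory and date it as added after data collection, since recruitment has closed and analysis is under way; it cannot be called pre-specified.
3. In the lagged models, adjust only for covariates measured before the lagged randomisation. Previous-day completion, a planned covariate, is post-treatment there.
4. Report estimates with confidence intervals, and do not use the sign of the summed effect as a decision rule. In simulation at trial size, that rule would pass a harmful strategy in 43% (c = 2) or 18% (c = 3) of runs and reject a beneficial one in 34% (c = 1). State that a wide interval means long-term benefit has not been established.

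The cost is a change of wording and a few extra models on existing data. The drawback is that their estimates, above all the sum, will be imprecise.

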#### Primary and Secondary Analyses

Our primary analyses will concern the following 2 hypotheses:

Providing the 4 pm reciprocity notification will yield a higher rate of full completion of the survey or active task on the same day than providing no intervention (*P*<.025).Among individuals who complete the survey, providing a postsurvey-completion meme or gif will yield a higher rate of completion of the survey or active task on the next day than not providing meme or gif reinforcement after survey completion (*P*<.025).

We selected these hypotheses as primary since our team found these hypotheses to be the most interesting scientifically. The 4 pm randomization is designed to address the question of whether a notification intended to facilitate reciprocation (by providing an inspirational message before self-report time) is useful, and the randomization of participants upon survey completion is designed to investigate whether providing a postdata collection reward increases data collection. Furthermore, we conjecture that these hypotheses have the greatest potential to be supported. In particular, as the 4 pm notification is proximal in time to the data collection (2 hours prior), there are fewer extraneous distracting circumstances that can occur during this short time window that would reduce the intervention effect. Both hypotheses also consider a contrast between an active agent (ie, the 4 pm notification or the meme) versus nothing. Since these 2 hypotheses are primary, we divide the standard *P* value of .05 by 2.

Our secondary analyses will concern the following 2 hypotheses:

The 6 pm reminder notification with an extra persuasive message will yield a higher rate of full completion of the survey or the active task on the same day than not providing the extra persuasive message.Among individuals who complete the active tasks, offering a postactive task-completion life insight will yield a higher rate of the full completion of the survey or active task on the next day than not offering a life insight after active task completion.

We consider the first hypothesis as secondary because the randomization for the 6 pm reminder is between 2 active agents (reminder with vs without a persuasive message). This implies that the additional effect of the persuasive messages may be small; thus, this hypothesis has a more exploratory nature. We consider the second hypothesis as secondary because data must accumulate before the visualizations in life insights become interesting. In addition, this hypothesis has a more exploratory nature because our life insights are only visualizations of past data; in the future, we aim for potentially more potent life insights using prediction tools [103,104].

For both primary and secondary analyses, we will control for the following 3 covariates to reduce variance in the outcome of self-input completion: (1) whether the survey or the active tasks were fully completed on the previous day, (2) whether SMS text messages or phone calls were made in the last 24 hours, and (3) whether the app was opened in the prior 72 hours outside when a survey or active task was completed. We will not include other baseline variables such as gender and age as covariates in the primary analyses because inclusion of a covariate uses up degrees of freedom. We also anticipate that the *within-person* covariate “whether the survey or active tasks were fully completed on the previous day” will capture some of the variance due to baseline gender or age. We will also not include time as a covariate in the primary analyses for the abovementioned reasons as well. Note that the statistical methods [83] will adjust the standard errors of the estimated effects to account for within-person correlation across time in the outcome. For more details about our primary analysis plan, please refer to the Center for Open Science document [102].

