#### Sample Size

We started recruiting for the study on August 21, 2017. Recruitment concluded on February 28, 2018. We recruited 73 participants for the study.

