### Limitations

Few limitations of this study are as follows: first, this study is not designed to confirm that the SARA is more effective than other apps in collecting substance use-associated data. This trial is only designed to optimize the further development of SARA. We believe that this is a necessary first step since the science of engagement in mHealth is currently in its infancy. This MRT will inform the selection and adaptation of engagement strategies, as well as the development of future versions of SARA, which can be used as an experimental arm in randomized trials.

Second, the current version of SARA is limited because the design primarily focused on increasing willingness, that is, to the extent a participant is motivated to engage in self-reporting. Prior literature suggests 2 other methods to influence engagement [44,77,108-111]: (1) need, namely an individual’s recognition that there is a discrepancy between his or her present state and a preferred future state, and (2) ability, namely the extent to which the individual has the knowledge, experience, skills, and capacity to engage in data collection. Although SARA is not currently designed to experiment with ability or need, SARA may influence them indirectly; for example, the reminder prompts before data collection can address forgetfulness and enhances the ability of participants to collect data. Furthermore, SARA sets clear goals, monitors engagement with aquarium progression, and offers timely feedback [112]. Thus, if participants become engaged with the aquarium or other incentives, they may recognize the need to engage.

A third limitation is the limited funding of the SARA mobile app, which is novel and exploratory in nature. Limited funding constrained our sample size. We also could not implement several features that were requested during user-centered design process; for example, better aesthetics of the fish, interactivity such as touching and interacting with fish, or personalization of such customizable background of the aquarium. In the future, we will use the results of this pilot study and apply for grants that can support larger studies and more resources for app development.

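### The two primary hypotheses are tested by single-step Bonferroni at P<.025 each; this is valid, but Holm's step-down holds the same .05 family-wise error and is never less powerful

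*Protocol article*

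**What the plan says.** The section Primary and Secondary Analyses of the protocol article opens with "Our primary analyses will concern the following 2 hypotheses". The first concerns the 4 pm notification, with the criterion attached to a higher rate of "completion of the survey or active task on the same day than providing no intervention (*P*<.025". The second concerns the meme or gif given after the survey, which is to yield a higher next-day rate "than not providing meme or gif reinforcement after survey completion (*P*<.025". The reason given for the threshold is "Since these 2 hypotheses are primary, we divide the standard" level of .05 by 2.

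No ordering of the hypotheses, step-down or recycling of alpha is mentioned. Sidedness is not stated, although the hypotheses are worded directionally ("Providing the 4 pm reciprocity notification will yield a higher rate of full completion").

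On size, the Sample Size section says "We recruited 73 participants for the study", and the Limitations section adds "Limited funding constrained our sample size". The Analysis Plan section points to a more detailed plan submitted on October 23, 2017, which is not shown. The Results section says that recruitment has closed and that analysis is in progress.

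**The concern.** Each primary test is held at .025 even after the other has been rejected. Error control does not require this. Once one of two hypotheses is rejected at .025, the remaining one can be tested at the full .05 without breaking the family-wise limit.

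The situation at stake is narrow. One strategy meets P<.025 and the other has a P value between .025 and .05. Under the stated rule the second strategy misses its criterion; under Holm both meet theirs. The trial's purpose is to choose among engagement strategies, so each primary hypothesis informs its own decision. The number of participants is fixed at 73, so a more efficient testing rule is one of the few ways left to gain power.

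**Working it through.** **Inputs.** Family-wise level .05, two hypotheses, threshold .025 each (Primary and Secondary Analyses). The article gives no power, effect size or completion rate, so power is assumed over a range. The base case is independent, two-sided tests with equal power; other cases follow below.

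**The plan's own figure.** .05 / 2 = .025, as stated. The sum of the two levels is .05. For independent tests the family-wise error is 1 − (1 − .025)² = .0494. The stated rule controls the error.

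**Holm for two tests.** Compare the smaller P with .025. If it is significant, compare the larger with .05.

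*Error control under any dependence:*
- Both nulls true: a false rejection needs the smaller P to pass .025, which has probability at most .025 + .025 = .05.
- One null true: that null can be rejected only if its own P passes .05, which has probability at most .05.
- Neither null true: no false rejection is possible.

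*Never less powerful:* any P below .025 is rejected under both rules. In simulation (2,000,000 draws per setting, correlation 0 and 0.3, one- and two-sided) there was no case in which Bonferroni rejected and Holm did not. With both nulls true, the two-sided family-wise error was the same for both rules: .0495 at correlation 0 and .0486 at correlation 0.3.

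**Size of the gain.** Let b be the power of one test at .025 and q its power at .05, where q = Φ(2.241 + z_b − 1.960) apart from a negligible opposite tail.

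- Power per hypothesis under Holm: b + b(q − b)
- Both rejected: b² under Bonferroni, b² + 2b(q − b) under Holm
- At least one rejected: 1 − (1 − b)² under both rules

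Example at b = .60: q = Φ(2.241 + 0.253 − 1.960) = .704. Power per hypothesis is .60 + .60 × .104 = .662. Both rejected is .36 + 2 × .60 × .104 = .484 (unrounded q).

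| b | q | Per hypothesis, Holm | Gain | Both: Bonferroni → Holm | Gain | At least one (both rules) |
|---|---|---|---|---|---|---|
| .20 | .288 | .218 | .018 | .040 → .075 | .035 | .36 |
| .30 | .404 | .331 | .031 | .090 → .152 | .062 | .51 |
| .50 | .611 | .555 | .055 | .250 → .361 | .111 | .75 |
| .60 | .704 | .662 | .062 | .360 → .484 | .124 | .84 |
| .70 | .790 | .763 | .063 | .490 → .616 | .126 | .91 |
| .80 | .869 | .855 | .055 | .640 → .751 | .111 | .96 |
| .90 | .941 | .937 | .037 | .810 → .884 | .074 | .99 |

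**One strategy truly without effect.** The effective strategy gains only .025 × (q − b): .0026 at b = .60 and .0017 at b = .80. The false-positive rate for the null strategy becomes .025 + .025b: .040 at b = .60 and .045 at b = .80, up from .025. In simulation at b = .80 it was .044 to .048 across correlation 0 and 0.3 and both sidedness choices. All of these are within .05.

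**Sensitivity.** At correlation 0.3 (two-sided, b = .80) power per hypothesis is .850 and both rejected goes from .666 to .766. With one-sided tests the same formulas give slightly larger gains; at b = .80 they give .861 per hypothesis and .762 for both.

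**The case against.** The strongest reply is that nothing here is wrong. Bonferroni is valid, a reason is given, and it comes with simultaneous 97.5% intervals that agree with the test decisions. That is a real advantage in a trial that also wants to report how large the effects are (Future Work). This stands. A reader might infer that the plan miscontrols error or contains a mistake; it does neither.

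The second reply is about timing. The detailed plan was lodged in October 2017, the trial has ended and analysis is in progress. Moving to a more liberal rule now could look like an attempt to rescue a P value between .025 and .05, the only region where the rules differ. This also stands, and it makes the change conditional.

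Third, the gain depends on both strategies working. That is not assured: the section on the 30-day trial itself allows that push notifications may lower engagement. If one effect is null, Holm brings the other almost nothing. This stands and is shown above.

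Two stronger readings are not supported. One is that a second result between .025 and .05 would be discarded: the article does not say how such a result will be treated, and the Limitations section presents the study as a step in developing the app. The other is that the absence of a power statement is itself a defect: the article condenses a longer plan that is not shown.

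**Conclusion.** The point holds as a low-cost gain in efficiency, not as an error. That Holm controls the family-wise error at .05 and never rejects less than Bonferroni rests on no assumption about power, dependence or sidedness. The size of the gain does: about 2 to 3 percentage points per hypothesis at 20-30% power, about 4 to 6 at 50-90%, and about 7 to 13 for rejecting both at 50-90%. These figures assume equal power and independent two-sided tests. The chance of at least one positive primary result is unchanged. Whether the change can still be made depends on whether the primary comparisons have been seen, which the article does not say.

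**What to change.** Replace the two fixed .025 criteria by one sentence: *The smaller of the two primary P values is compared with .025; if it is significant, the larger is compared with .05 (Holm, family-wise .05).* Keep whatever sidedness the detailed plan specifies; this change should not settle that question.

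Record the change with a date before anyone sees a primary outcome comparison. If results have already been seen, keep Bonferroni as the confirmatory rule and report Holm only as supplementary.

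The cost is one sentence and a dated record, with no new data or model. The downside is in the intervals: a simple 97.5% interval may include no effect for a hypothesis rejected at the second step. If such intervals are reported, label them as not matching the step-down decision.
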